**Figure 1 BMJOPEN2016012044F1:**
[figure not shown]
The cohort construction for cohort type A, designed to eliminate immortal time bias. A patient will enter the cohort for a given treatment when they first become ‘at risk’ of the condition the treatment is used for or, in the case of no period ‘at risk’, when they are first diagnosed with the condition (see table 2). For example, when they are diagnosed as at ‘at risk of’ hypertension or, in the case of no period ‘at risk’, when they receive a diagnosis of hypertension. We define cohort entry in this way to avoid excluded immortal time bias that can occur when cohort entry is determined by treatment variation over time.^33^
^34^ Immortal time is the period during follow-up when the outcome cannot occur. Consider the hypertension example above, suppose we started following the treated patients in our cohort from the date of their first prescription of a treatment for hypertension and the untreated patients from a matched date. This would make it impossible for the treated patients to have an outcome, such as dementia, prior to their first prescription. Consequently, patients in this group would all have a period before treatment, when they could not be diagnosed with dementia, that is, they could not experience the outcome. This period is their immortal time, and it must be correctly attributed to the ‘unexposed’ group so that their outcome is not falsely attributed to their exposure. To do this, patients in the ‘exposed’ and ‘unexposed’ groups must be followed-up and compared from the same start date. In this cohort, we are minimising excluded immortal time by following patients from either a test result or diagnosis where possible. In order to capture all relevant patients, we will allow those receiving treatment without a recorded diagnosis to be included as it is assumed treatment suggests a diagnosis.

10.1136/bmjopen-2016-012044.supp1supplementary file

10.1136/bmjopen-2016-012044.supp2supplementary file

10.1136/bmjopen-2016-012044.supp3supplementary file

Follow-up for cohort A will start on the first date a patient is diagnosed with the condition the treatment is used for or ‘at risk’ of that condition (see table 2 and online supplementary files 1–3.) Follow-up will end with the earliest of a relevant neurodegenerative disease diagnosis, death or censoring due to the end of registration at a CPRD general practice.

#### Cohort B

In this analysis, we will compare different drug subclasses that exist for a given treatment (listed in box 1). To do this, we will create a cohort of all patients who were prescribed a treatment and categorise them by the drug subclass they initially received. This will allow us to compare the outcomes for each of the resulting subgroups. For each treatment, we have defined the most frequently prescribed subclass as the control (indicated in box 1). In the primary analysis of this cohort, we will exclude patients initially prescribed the control subclass if they receive another subclass of the same treatment at the same time, however we do not expect this to be a common. We will explore the outcomes of individuals prescribed multiple subclasses, other than that specified above, in a sensitivity analysis.
Box 1The drug subclasses of interest for each treatment group with the control treatments indicatedTreatments for hypertensionBeta-adrenoceptor blocking drugs (control)Angiotensin-converting enzyme inhibitorsThiazides and related diureticsCalcium channel blockersLoop diureticsAlpha-adrenoceptor blocking drugsCentrally acting antihypertensive drugsAngiotensin-II receptor antagonistsVasodilator antihypertensive drugsPotassium-sparing diuretics and aldosterone antagonistsTreatments for hypercholesterolaemiaStatins (control)FibratesBile acid sequestrantsOmega-3 fatty acid compoundsEzetimibeNicotinic acid groupTreatments for type 2 diabetesBiguanides (control)SulphonylureasOther antidiabetic drugs

Follow-up for cohort B will start on the date of first eligible prescription as determined by a product code (see the treatment code lists in online supplementary files 1–3). Follow-up will end with the earliest of a relevant neurodegenerative disease diagnosis, death or censoring due to the end of registration at a CPRD general practice.

#### Cohort C

For each neurodegenerative disease group of interest, we will create a cohort of individuals with a read code indicating this outcome (see online supplementary file 4) or a product code indicating they received treatment for the outcome (see online supplementary file 5). These cohorts will be used to investigate the associations of neurodegenerative disease progression with exposure to one of the three treatment groups of interest: treatments for hypertension, treatments for hypercholesterolaemia and treatments for type 2 diabetes. We will investigate both exposure before and after the diagnosis of a neurodegenerative disease. For all of the treatments we consider, each cohort will be split into ‘exposed’ and ‘unexposed’ groups. In the analysis, individuals in the ‘exposed’ group, that is, those who were prescribed the treatment under investigation, will be compared with individuals in the ‘unexposed’ groups, that is, those who did not receive the treatment.

10.1136/bmjopen-2016-012044.supp4supplementary file

10.1136/bmjopen-2016-012044.supp5supplementary file

Follow-up for cohort C will start with the first recorded read code indicating AD or other neurodegenerative disease (see online supplementary file 4) or, in the absence of a diagnosis, the first recorded product code indicating they received treatment for a neurodegenerative disease (see online supplementary file 5). Follow-up will end with the earliest of death or censoring due to the end of registration at a CPRD general practice.

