### Sample selection

We will investigate the incidence and progression of AD, NADD, PD and ALS. Our investigations into the incidence will focus on treatments which are reported to be cerebroprotective and are currently prescribed for hypertension,^6^ hypercholesterolaemia^7^
^8^ and type 2 diabetes.^9^ For each treatment, we will conduct two analyses. The first will compare treated to untreated individuals with similar indications—this is cohort A. The second will compare the outcomes of individuals given different subclasses of specific medications—this is cohort B. We will also investigate progression using a third cohort, cohort C. Progression will be defined as the postdiagnosis survival of a patient. For each neurodegenerative disease group of interest, we will determine the effects on progression of the three possible new treatments. In cohort C, exposure will be defined in two ways: (1) using patients being prescribed these drugs at the time of diagnosis of their neurodegenerative disease; and (2) using those issued new prescriptions postdiagnosis. The structure of these three cohorts is summarised in table 1 and further explained in the text that follows. All of the cohorts rely on defined diagnoses and exposures, which are recorded in the CPRD through the use of Read and product codes, respectively. Read codes uniquely identify clinical terms recorded by the general practitioner (GP) during a consultation, while product codes uniquely identify prescriptions issued. Both types of code are recorded with a date, and this will be used to determine the dates of diagnosis and exposure required to define the cohorts.

**Table 1 BMJOPEN2016012044TB1:** Comparison of the three cohort types

	Cohort A	Cohort B	Cohort C
Purpose	To investigate incidence by comparing treated and untreated individuals.	To investigate incidence by comparing the different drug subclasses of each treatment.	To investigate progression by comparing treated and untreated individuals.
Number of cohorts required	There will be three cohorts of this type, one for each treatment of interest.	There will be three cohorts of this type, one for each treatment of interest.	There will be three cohorts of this type, one for each of dementia (AD or NADD), PD and ALS.
Exposures	Treatments for hypertension, hypercholesterolaemia and type 2 diabetes.	Treatments for hypertension, hypercholesterolaemia and type 2 diabetes.	Treatments for hypertension, hypercholesterolaemia, and type 2 diabetes.

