Start of follow-up (index date)	Date at first risk of the condition the treatment is used for or date of first diagnosis of the condition itself if there was no preceding period ‘at risk’.	Date of first prescription of a treatment of interest.	Date of first diagnosis of neurodegenerative disease of interest.
Outcome	Diagnosis of neurodegenerative disease of interest.	Diagnosis of neurodegenerative disease of interest.	Death.
Exclusion criteria	Individuals with <12 consecutive months of records prior to cohort entry.	Individuals prescribed treatment and control medications at the same time or with <12 consecutive months of records prior to cohort entry.	Individuals with <12 consecutive months of records prior to cohort entry.
Statistical analysis	Conventional regression, propensity score regression, instrumental variable analysis and marginal structural models.	Conventional regression, propensity score regression, instrumental variable analysis and marginal structural models.	Conventional regression, propensity score regression and marginal structural models.

AD, Alzheimer's disease; ALS, amyotrophic lateral sclerosis; NADD, Non-Alzheimer's disease dementias; PD, Parkinson's disease.

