### Confounding

We have identified two key sources of confounding in our study: confounding by indication and time-dependent confounding. To address the former, we will use four different statistical methods, which have different approaches for modelling confounding. Through examination of these approaches, we hope to highlight any uncontrolled confounding that may be leading to false conclusions about drug effect. We will also account for confounding by indication in the construction of our cohorts. Consider cohort A, where we compare ‘exposed’ and ‘unexposed’ groups of individuals. Drawing the ‘unexposed’ group from the full population can introduce bias as they are likely to be in better health. We will avoid this by defining cohort entry on the basis of first test or recording of a relevant read code so the ‘exposed’ and ‘unexposed’ groups will have more in common. In addition to this, we will address time-dependent confounding in our study. This will be carried out using marginal structural models, which can allow for time-dependent confounding and treatment switching between products.

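### Cohort C compares treated patients with all untreated patients who have the same neurodegenerative disease, with or without the drug's indication, so its survival HRs are open to confounding by indication

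*Protocol article*

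**What the plan says.** The Cohort C section of the protocol article defines entry by the neurodegenerative disease alone: "we will create a cohort of individuals with a read code indicating this outcome", or a product code for its treatment. The cohort is then split for each drug class into those prescribed it and the rest, "that is, those who did not receive the treatment". In Table 1 the purpose is "To investigate progression by comparing treated and untreated individuals", the outcome is death, and the only exclusion is "Individuals with <12 consecutive months of records prior to cohort entry". Sample selection is explicit about the endpoint: "Progression will be defined as the postdiagnosis survival of a patient".

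Cohort A is built differently. Sample selection says of its two incidence analyses: "The first will compare treated to untreated individuals with similar indications". The Cohort A section gives confounding by indication as the reason, and the Confounding section repeats it: drawing the unexposed "group from the full population can introduce bias as they are likely to be in better health". That section says the construction of the study's cohorts will account for confounding by indication, then describes only cohort A.

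For methods, Table 1 gives cohort C "Conventional regression, propensity score regression and marginal structural models". Cohorts A and B have instrumental variable analysis as well.

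**The concern.** Within cohort C, patients given antidiabetic drugs are set against all untreated patients with the same neurodegenerative disease, including those without diabetes. The same construction applies to antihypertensive and lipid-lowering drugs. If the indication itself affects survival, the HR reflects both the indication and the drug. An indication that raises mortality could hide or reverse a real benefit; one associated with lower mortality would make an inert drug look protective. The large sample does not help, because it only narrows the interval around the confounded value. The Introduction says the findings will be used to prioritise drugs for trials, so the error would carry forward.

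**Working it through.** **1. Is anyone left out of cohort C for lacking the indication?** The Study size section defines the minimum sample size as the smallest exposed group plus the control group. Dividing it by the cohort size in Table 3:

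| Row | Minimum / cohort | Ratio |
|---|---|---|
| B, hypertension | 269 808 / 1 018 519 | 0.265 |
| B, hypercholesterolaemia | 788 479 / 808 687 | 0.975 |
| B, type 2 diabetes | 158 775 / 200 800 | 0.791 |
| C, dementia | 105 471 / 105 471 | 1.000 |
| C, PD | 20 686 / 20 686 | 1.000 |
| C, ALS | 2227 / 2227 | 1.000 |

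In cohort C, exposed plus control is the whole disease cohort in every row. This agrees with the text: no restriction on indication is applied.

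**2. Can the stated detectable HRs be reproduced?** Schoenfeld's formula is D·p(1−p) = (z_α + z_power)² / (ln HR)², where D is deaths and p the exposed share. With two-sided 0.05 and power 0.80 (which the article prints as β), the numerator is (1.960 + 0.842)² = 7.85. The implied D·p(1−p) is 1535.5 for HR 0.931, 404.7 for 0.870 and 30.1 for 0.600. For dementia this means an exposed share of about 1.5% if all die, 3.0% if half die and 5.1% if 30% die. The article gives neither D nor p, and supplementary files 6 to 8 are not shown, so the figures are attainable but cannot be verified. The concern does not depend on them.

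**3. What else could control for the indication?**
- Exposures assigns severity of the treatment indications to instrumental variable analysis, and Covariates looks to methods such as it for unmeasured confounding. Cohort C does not have it.
- Covariates lists body mass index, smoking, alcohol, deprivation, coronary disease, bypass surgery, cerebrovascular disease, the Charlson Index and consultation rate. It names no diagnosis of hypertension, hypercholesterolaemia or diabetes, and no blood pressure, lipid or glucose measure.
- The propensity score is built from that same list.
- Statistical methods concedes that marginal structural models assume no unmeasured confounders.

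**4. How large could it be?** The documents give no inputs, so these are assumptions: the drug has no effect, all treated patients have the indication, the indication multiplies the death hazard by h, and a share u of the untreated has it. Then the unadjusted HR ≈ h / (u·h + 1 − u).

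| h | u = 20% | u = 50% | u = 80% |
|---|---|---|---|
| 1.10 | 1.08 | 1.05 | 1.02 |
| 1.25 | 1.19 | 1.11 | 1.04 |
| 1.50 | 1.36 | 1.20 | 1.07 |

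For example, 1.25 / (0.2 × 1.25 + 0.8) = 1.25 / 1.05 = 1.19. The mirror image of the detectable HR is 1 / 0.931 = 1.074. Five of the six values at u = 20% and 50% exceed it; none at 80% does. At h = 1.10 and u = 20%, a true HR of 0.931 would appear as about 0.931 × 1.078 = 1.00.

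**The case against.** Four points on the other side deserve weight.

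*The protocol does not reject this comparator.* A reader might infer that cohort C makes exactly the comparison ruled out for cohort A. It does not. What the protocol rejects is an unexposed group from the full population. In cohort C everyone has the same neurodegenerative disease and is followed from its diagnosis. This stands, but sharing that disease does not equalise the drug's indication, so the protocol's reasoning extends to cohort C.

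*Adjustment is planned.* Vascular history, the Charlson Index, propensity matching, and weights on comorbidities and concurrent treatments should remove part of the difference. Charlson may capture some of the diabetes contrast, and Exposures mentions exploring disease control with marginal structural models, without naming a measure. It would therefore be wrong to say that the HR will simply estimate the effect of having diabetes or hypertension. What remains is that all these tools work through measured covariates, and those named omit the indication.

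*The size is assumed.* A reader might take a high mortality ratio and a low share of untreated patients with the indication, and conclude that the bias is very large. Nothing in the documents supports such inputs after adjustment. For hypertension and cholesterol, the Table 2 thresholds are low (systolic from 120 mm Hg, total cholesterol from 4 mmol/L), so most untreated patients may qualify. With 70% to 90% qualifying and mortality ratios of 1.2 to 2.0, the formula gives only about 1.02 to 1.18.

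*Endpoint and methods are stated openly.* Progression is defined as survival, cause of death from ONS is already planned, and Table 1 shows that cohort C has no instrumental variable analysis. None of these is an error in itself. The last matters only because other sections rely on that analysis.

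**Conclusion.** The concern holds as a design weakness that should be corrected. Entry, comparator, exclusions and methods for cohort C are all stated, and together they leave confounding by indication without the safeguards the protocol applies elsewhere, although the Confounding section speaks of the cohorts in general. The cohort C HRs may mix the mortality effect of the indication with any drug effect.

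The size cannot be derived from the documents. Under the assumptions shown, with 20% to 50% of the untreated having the indication, a null drug gives an HR of about 1.05 to 1.36 before adjustment. Adjustment would be expected to reduce this, and it moves towards 1 as more untreated patients have the indication. The documents do not establish that the adjusted results will be biased by any particular amount, or in which direction for each drug class.

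**What to change.** - For each treatment, make the primary cohort C comparison treated versus untreated among patients who have the indication. Use the diagnosis-level criteria in Table 2, not the at-risk bands, which would leave much of the contrast in place. Every treated patient meets the treatment product-code criterion by definition, so state how patients who qualify only that way are handled.
- For exposure at diagnosis, assess the indication at the index date. For new post-diagnosis prescriptions, assess it as it arises after diagnosis, with treated and untreated patients alike entering the comparison from that point. Requiring it at or before the neurodegenerative diagnosis would drop part of this second exposure group.
- Add pre-index blood pressure, lipid or glycaemic measures, where recorded, to the covariates and propensity model.
- Keep the unrestricted comparison as a sensitivity analysis, restate the cohort C detectable HRs, and say in the Confounding section how confounding by indication is handled in cohort C.

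**Cost.** The code lists already exist. The unexposed groups shrink and more covariate data will need imputing. As an illustration, hold the number exposed fixed at the value implied by Table 3 and assume that 30% to 80% die and 20% to 70% of the cohort has the indication. The detectable HR then becomes 0.922 to 0.931 for dementia (stated 0.931), 0.846 to 0.869 for PD (0.870) and 0.565 to 0.599 for ALS (0.600). The loss is larger if fewer have the indication: at 10%, dementia falls to 0.905 to 0.925, PD to 0.782 to 0.853 and ALS to 0.503 to 0.573.

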#### Outcomes

For incidence, we will identify the neurodegenerative disease outcomes (AD, NADD, PD and ALS) by the first record of a relevant read code (see online supplementary file 4) or the first record of a product code indicating treatment for the neurodegenerative disease (see online supplementary file 5). For incidence and progression, we will identify deaths using linked Office of National Statistics (ONS) data.

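### Cohort C dates follow-up from the Read code and falls back on the treatment code only when no diagnosis is recorded, so for patients treated first the index date depends on surviving and staying registered until coded

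*Protocol article*

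**What the plan says.** Cohort C studies progression, with death as the outcome: "Progression will be defined as the postdiagnosis survival of a patient". A patient qualifies through a Read code "or a product code indicating they received treatment for the outcome".

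The start of follow-up ranks these two sources: "Follow-up for cohort C will start with the first recorded read code indicating AD or other neurodegenerative disease", "or, in the absence of a diagnosis, the first recorded product code indicating they received treatment for a neurodegenerative disease". The end is the same for everyone: "Follow-up will end with the earliest of death or censoring due to the end of registration at a CPRD general practice".

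Three other places bear on the date:

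- Table 1 gives the cohort C index date as "Date of first diagnosis of neurodegenerative disease of interest" and does not mention the fallback.
- The Outcomes section identifies the same diseases, for incidence, "by the first record of a relevant read code (see online supplementary file 4) or the first record of a product code indicating treatment". Neither source is ranked above the other.
- The Sample selection section ties cohort C exposure to the diagnosis. The first definition is "using patients being prescribed these drugs at the time of diagnosis of their neurodegenerative disease"; the second is new prescriptions after diagnosis.

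The Bias section undertakes to follow exposed and unexposed patients from a consistent index date in order to limit immortal time. It prefers a test result or Read code where possible and also admits treated patients who have no recorded diagnosis.

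**The concern.** Whether a diagnosis is absent cannot be known on the day of the first disease-treatment prescription. Take two patients first prescribed such a drug in January 2008. One is Read-coded in January 2009 and starts follow-up in 2009. The other dies uncoded in mid-2008 and starts in January 2008. The first loses a year that was necessarily event-free; the second keeps both the short interval and the death.

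With death as the outcome, this raises the death rate among treatment-first patients. If exposed patients are coded sooner or later than unexposed patients, the distortion differs between the groups and carries into the hazard ratio. Sooner coding of the exposed would look like a survival benefit, in a study that claims power for small effects.

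The same date decides whether an index drug counts as present at diagnosis or as new afterwards. A drug started between the treatment code and the Read code changes category according to which code is taken as the diagnosis.

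**Working it through.** **Step 1: the wording.** Outcomes of the cohort C rule for patients with a disease-treatment code before any Read code:

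| What happens after the first treatment code | Start of follow-up | Interval between the codes |
|---|---|---|
| Read code recorded later | Read code | dropped, event-free by construction |
| Death before any Read code | treatment code | kept, with the death |
| Leaves the practice before any Read code | treatment code | kept, no event |

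Patients who are Read-coded first are unaffected.

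**Step 2: death rate among treatment-first patients.** The plan states no figure to reproduce, and it gives neither the share treated first, nor the delay, nor the death rate. All inputs here are assumptions. Let L be a constant death rate and R = 1/(mean delay to Read code), with no censoring.

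- Person-time per patient from the earlier code: 1/L.
- Person-time removed by the rule: R/(L+R)².
- Inflation of the death rate: (1/L) ÷ [1/L − R/(L+R)²].
- Share dying before a Read code: L/(L+R).

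With L = 0.2 per year, 1/L = 5 years:

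- Mean delay 1 year (R = 1): removed 1/1.44 = 0.694; inflation 5/4.306 = 1.161; 16.7% die uncoded.
- Mean delay 2 years (R = 0.5): removed 0.5/0.49 = 1.020; inflation 5/3.980 = 1.256; 28.6% die uncoded.

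Over L from 0.1 to 0.3 and mean delays from 0.25 to 2 years, the inflation runs from 1.02 to 1.31. Starting at the earlier code gives 1.00.

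**Step 3: exposed against unexposed, no true effect.** Suppose the delay is 1 year in the exposed and 2 years in the unexposed. Among treatment-first patients alone the rate ratio is 1.161/1.256 = 0.924. If a fraction f of the whole cohort is treated first, the ratio is (5 − 1.020f)/(5 − 0.694f):

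| f | Unexposed person-years | Exposed person-years | Ratio |
|---|---|---|---|
| 10% | 4.898 | 4.931 | 0.993 |
| 30% | 4.694 | 4.792 | 0.980 |
| 50% | 4.490 | 4.653 | 0.965 |

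Swapping the delays reverses the direction: at f = 30% the ratio is 4.792/4.694 = 1.02.

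**Step 4: Cox models on simulated null data.** These used 60,000 patients per run, L = 0.2 and uniform censoring over 0 to 10 years. Each pair shows the hazard ratio from the earlier code, then under the plan's rule.

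| Mean delay, exposed v unexposed | f = 10% | f = 30% | f = 50% |
|---|---|---|---|
| 1 v 1 year | 1.000, 1.000 | 0.983, 0.982 | 1.002, 1.002 |
| 1 v 2 years | 1.017, 1.011 | 1.016, 0.999 | 1.012, 0.981 |
| 0.5 v 2 years | 1.006, 0.994 | 1.003, 0.968 | 1.008, 0.945 |

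The shift within each pair is what matters; departures of the first figure from 1 are sampling noise. Equal delays leave the hazard ratio essentially unchanged. Delays of 1 v 2 years shift it by about 1% to 3%, slightly less than in Step 3 because of censoring. The wider 0.5 v 2 contrast shifts it by about 1% to 6%. If 30% of treatment-first patients are assumed never to be coded, the ratios for 1 v 2 years shrink to roughly 0.995, 0.99 and 0.98.

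**The case against.** - **The word ever is not in the text.** Absence of a diagnosis could mean that none is recorded when treatment is first seen. Follow-up would then start at the earlier code and there would be no defect. This is possible but is not the natural reading, and the rule it implies is the one recommended here, so the sentence still needs changing.
- **The Read-code preference is deliberate.** The Bias section states it, and the strengths and limitations list acknowledges imperfect electronic case definitions and promises sensitivity analyses. Read codes may well be more specific. That justifies a preference, but not a start date that depends on later events.
- **A reader might infer a flat contradiction with the Outcomes section.** The documents do not support that. The section names both sources without ranking them and does not say that the earlier one counts. The dates may differ; they are not shown to. Table 1 can be read as shorthand. Because the incidence and progression cohorts are analysed separately, a differing date does limited harm within any one analysis.
- **A reader might infer a demonstrated, spurious survival benefit.** This is not supported either. It needs coding delays that differ by exposure. More frequent consultation by patients with chronic conditions makes earlier coding plausible, but the document does not show it, and the planned adjustment for consultation rate may reduce any such difference. Later coding of the exposed would bias the other way.
- **The ratio of 0.924 should not be set beside the detectable HR of 0.931 for dementia in Table 3.** The first concerns treatment-first patients only; the second refers to the whole cohort. None of the whole-cohort illustrations above reaches 0.931.

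**Conclusion.** The point holds in a limited form. On its natural reading, the cohort C rule makes the index date of treatment-first patients depend on later survival and registration. It overstates their death rates and departs from the protocol's own commitment to a consistent index date.

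Bias in the hazard ratio is conditional. It is near nil with equal delays and about 1% to 4% across the whole cohort with assumed mean delays of 1 v 2 years and 10% to 50% treated first. It is larger with a wider contrast, smaller if many treatment-first patients are never coded, and opposite in sign if the exposed are coded later. The share treated first, the delays and the death rate are all assumptions. The change is worth making because it is cheap and the protocol emphasises its power for small effects, but a material bias has not been demonstrated.

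**What to change.** Start cohort C follow-up at the earlier of the first relevant Read code and the first relevant product code. State that single disease date in the Cohort C section, Table 1 and the Outcomes section, and date both the at-diagnosis and the postdiagnosis exposure definitions from it.

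Add one sensitivity analysis based on Read codes, in either of two forms: restrict to patients with a Read code and no earlier disease-treatment product code, or index at the Read code and exclude product-only patients. Both set day zero from what is known on that day.

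The cost is a sentence in the cohort definition, matching edits in the two other places and a change to the date-derivation code. No new data are needed. The downside is that some patients will be indexed on a drug prescribed for another reason. Their number cannot be judged from the document, and the sensitivity analysis shows whether they matter.
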